### Interim analyses {21b}

Not applicable, because no interim analyses are planned because there are no anticipated risks to participation in this study.

### Methods for additional analyses (e.g., subgroup analyses) {20b}

#### Cost-effectiveness analysis (CEA)

The cost-effectiveness of the novel care approach compared with usual care will be determined by dividing the difference in the mean costs (in Euros) by the difference in the mean health outcomes (in QALYs) to estimate the incremental cost-effectiveness ratio (ICER). For this trial-based, short-term cost-effectiveness analysis (CEA) with 1-year time horizon bootstrapping will be applied to determine the uncertainty in this ICER. The cost-effectiveness analysis for a lifetime time horizon will be model-based, using data from the literature as well as the trial data. Here, probabilistic sensitivity analysis will be applied to assess how uncertainty in model input parameters results in uncertainty in the ICER. The results will be presented in incremental cost-effectiveness planes and cost-effectiveness acceptability curves.

#### Methods in analysis to handle protocol non-adherence and any statistical methods to handle missing data {20c}

Between-group differences in the proportion of participants who adhere to the use of their orthopedic shoes, that is, who take at least 80% of their total daily steps with orthopedic shoes, will be tested in an intention-to-treat analysis using a generalized linear mixed model (GLMM) which can inherently deal with data missing at random.

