### Criteria for discontinuing or modifying allocated interventions {11b}

Participants can leave the study at any time for any reason if they wish to do so without any consequences. The investigator can also decide to withdraw a participant from the study for urgent medical reasons. The outcomes will no longer be collected, and participants’ data that have been collected up to that moment will be included in the analysis. If participants drop out of the study, additional participants will be included until *N* = 220.

Given the low risk of the intervention, there are no criteria set for premature termination of the study, because this is not to be expected.

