#### Proportion participants being adherent

The main study parameter is the proportion of participants who adhere to wearing their orthopedic shoes, defined as minimally 80% of steps taken with orthopedic shoes. The level of adherence (see the “Level of adherence to orthopedic shoes” section) will be based on log data from temperature microsensors in the orthopedic shoes and data from the activity monitors provided to all participants over two 1-week periods measured at time point “T1” and time point “T3” (Table 2). The proportion of adherent participants will be objectively determined based on the combined level of adherence of the two measurements (the mean of time point “T1” and time-point “T3”).

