#### Level of adherence to orthopedic shoes

The level of adherence to the use of orthopedic shoes will be determined by the percentage of total steps during the full recording period that the orthopedic shoes were worn and will be calculated as follows:
$$ \mathrm{Adherence}=\frac{\Sigma \kern0.5em \mathrm{steps}\ \mathrm{wearing}\ \mathrm{orthopaedic}\ \mathrm{shoes}}{\Sigma \kern0.5em \mathrm{steps}}\times 100 $$

Total steps wearing orthopedic shoes will be based on log data from temperature microsensors in the orthopedic shoes of all participants, and total steps will be based on using the data from the activity monitors over two times 1 week period measured at time point “T1” and time point “T3” (Table 2).

Adherence to wearing orthopedic shoes and daily step count will be assessed using raw data from the temperature microsensors using and processed by MATLAB (The MathWorks Inc., Natick, MA, USA). Participants will be included in the analyses only if at least four complete days of recording, including one weekend day, are available [14]. When both the temperature microsensor and the step activity monitor show activity during recording, it will be assumed that the participant walked with the orthopedic shoes. If only step activity is recorded, it will be assumed that the participant was walking barefoot or walking in non-prescribed shoes.

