#### Primary study outcome

Between-group differences in the proportion of participants who adhere to the use of their orthopedic shoes, that is, take at least 80% of their total steps with orthopedic shoes will be tested using a generalized linear mixed model (GLMM). A logistic link function will be used for the binary outcome on participant level (adherent yes/no) and random effects for podiatrists will be included.

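### The statement that the GLMM inherently handles data missing at random does not fit a model with one yes/no record per participant: as described, it is a complete-case analysis under an intention-to-treat label

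*Protocol article*

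**What the plan says.** All statements are in the protocol article.

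- **Missing data (section {20c}).** The primary comparison "will be tested in an intention-to-treat analysis using a generalized linear mixed model", and the model is described as a "generalized linear mixed model (GLMM) which can inherently deal with data missing at random".
- **Outcome construction (Proportion participants being adherent).** Adherence is measured in two separate weeks. Each participant's status "will be objectively determined based on the combined level of adherence of the two measurements", that is, from the mean of the two, cut at 80% of steps.
- **Model (Primary study outcome).** It has a logistic link, and a "binary outcome on participant level (adherent yes/no) and random effects for podiatrists will be included". No participant-level random effect and no repeated weekly record is described.
- **Recording rule (Level of adherence to orthopedic shoes).** "Participants will be included in the analyses only if at least four complete days of recording, including one weekend day, are available".
- **Withdrawal (section {11b}).** "The outcomes will no longer be collected, and participants’ data that have been collected up to that moment will be included in the analysis". Dropouts are replaced until 220 are included.

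**The concern.** A mixed model makes use of incomplete participants when they still have records in the likelihood, for example one of two weekly values. Here the weeks are combined before modelling, so a participant either has the single record or has none. The safeguard in section {20c} is then absent where it would be needed, namely when missingness depends on something observed but outside the model, such as the other week's adherence, sensor-recorded wearing time or a baseline factor.

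A usable week needs the participant to wear a monitor day and night, return it, and bring the sensor-equipped shoes for read-out. These behaviours are close to the one being measured, so missingness related to adherence is plausible. The trial is open-label, so a difference between arms in that relation cannot be ruled out. At stake are the primary comparison, the reported adherence proportions, and a reader's belief that missing data have been dealt with when they have been deleted.

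The recording rule is a second problem. It decides after enrolment who is analysed, which does not sit with the intention-to-treat label.

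**Working it through.** **1. The plan's own sample size.** Inputs from section {14}: 40% vs 60%, two-sided alpha 0.05, power 0.80, ICC 0.01. Section {16a} gives 20 podiatrists, so about 10 participants each at 200.
- Per arm, unpooled variance: (1.960 + 0.842)² × (0.24 + 0.24) / 0.20² = 7.849 × 0.48 / 0.04 = 94.2.
- Design effect: 1 + 9 × 0.01 = 1.09. Total: 2 × 94.2 × 1.09 = 205.3, close to the stated 200. Power at 200 is 0.79.
- Loss that 220 can absorb while keeping 200: 1 − 200/220 = 9.1%. The stated expectation is 10/171 = 5.8%.

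**2. What a missing record contributes.** Given the podiatrist effect, a participant with an observed outcome contributes p or 1 − p. One with a missing outcome contributes the sum over both possible values, p + (1 − p) = 1, and so drops out of the product. A simulated data set (20 podiatrists × 11 participants, about 15% of outcomes missing, 186 observed) confirmed this:

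| Fit | Log-odds ratio | −log-likelihood |
|---|---|---|
| All 220, missing integrated out | 0.78028 | 125.28868 |
| 186 complete cases | 0.78028 | 125.28868 |

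**3. Illustration with data that are missing at random given the first week.** Every rate here is an assumption. Weekly adherence has SD 0.25 (before truncation to 0–100%) and within-person correlation 0.6. The outcome is the mean of two weeks cut at 80%, and there is no true effect, with about 50% adherent in each arm. By simulation the population splits as follows:

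| | First week ≥80% | First week <80% |
|---|---|---|
| Adherent on the mean | 42.8% | 7.1% |
| Not adherent | 7.6% | 42.5% |

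In the intervention arm the record is lost with probability 5% if the first week is at least 80%, and 30% otherwise. In controls it is lost in 10% whatever the first week.
- Intervention, adherent and kept: 0.428 × 0.95 + 0.071 × 0.70 = 0.456.
- Intervention, all kept: 0.504 × 0.95 + 0.496 × 0.70 = 0.826.
- Complete-case proportion: 0.456 / 0.826 = 55.2%. Controls stay at 49.9%. Apparent difference: **about 5 points, against a true 0**.
- Using the first week (weighting the kept by 1/0.95 and 1/0.70): 0.428 + 0.071 = 49.9%, a difference of 0.

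The same rule applied to true proportions of 40% and 60% gives 40% vs about 65%, or 25 points against a true 20.

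**4. Same rule in both arms** (25% lost if the first week is below 80%, 5% otherwise). The 40% and 60% become 44.0% and 63.8%, a difference of 19.8 points. At 50% in both arms, both become 54.0%. The proportions shift and the contrast hardly moves.

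**5. Assumption-free limits.** For observed proportions of 40% and 60% with a fraction m missing in each arm, the difference among all participants lies between 0.20(1 − m) − m and 0.20(1 − m) + m.
- m = 6%: 0.188 ± 0.06, or 13 to 25 points.
- m = 15%: 0.170 ± 0.15, or 2 to 32 points.

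Counting all missing as non-adherent gives the centre values, 18.8 and 17.0 points.

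**The case against.** **The sentence is too general rather than false.** With one outcome per participant, analysing the observed records is valid when missingness depends only on variables in the model. This stands. The sentence needs qualifying, and multiple imputation also assumes data missing at random, only with more variables to make that credible.

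**Covariates and sensitivity analyses may sit in an unseen document.** This stands as far as it goes: the model description does not exclude covariates, and the absence of an imputation plan from an article is not the point. The point is a positive statement in the text about what the described model does.

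**The arms are handled alike.** Reminder calls and the chasing of unreturned monitors apply to all participants, and monitor visits are scheduled identically. The additional MI consultation is with the podiatrist, not at a monitor visit. This makes arm-different missingness less certain, without excluding it.

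**Stronger readings that the documents do not support:**
- *One missed week always loses the participant, so attrition will far exceed the plan.* The article does not say whether the four-day rule applies per week or over both, or whether one valid week yields an outcome. Section {11b} keeps data gathered before withdrawal, so one-week participants might be retained. They would then be judged on one week instead of the mean of two, and that would still not be the GLMM handling missing data.
- *The trial is underpowered because only 6% loss was allowed.* The step from 200 to 220 absorbs 9.1%.
- *The primary result is biased in favour of the novel care approach.* That needs missingness related to adherence differently by arm, for which the documents give no evidence.
- *Outcome collection should continue after withdrawal.* Stopping it is a conduct and consent rule. Further read-outs would need further visits and consent, and the error in section {20c} does not depend on it.

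**Conclusion.** The point holds. As described, the primary model contains one record per participant, and participants without it contribute nothing. That is exact and needs no assumed rates. The inherent handling of data missing at random therefore covers only missingness explained by arm and podiatrist (and any other covariate, if one is in the model). It does not cover missingness explained by the other week, wearing time or baseline factors left out. The recording rule conflicts with the intention-to-treat label, and the treatment of a single valid week is open.

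The size is not known. About 5 spurious points is an illustration that rests on the assumed loss rates, SD and correlation, and on loss that depends on the first week in one arm only. With equal dependence in both arms, the harm is mainly to the reported proportions, about 4 points in the example. The matter should be settled before the data are analysed because it concerns the primary outcome, but it is not evidence that the comparison will be wrong.

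**What to change.** 1. In section {20c}, replace the sentence on data missing at random with what the model assumes: participants without an outcome record are not used, and the result is valid if missingness depends only on the variables in the model.
2. In the section on the level of adherence, say that a week failing the four-day rule is missing, and that the participant stays in the analysis. This also settles how one valid week is handled.
3. Impute the weekly adherence level by multilevel multiple imputation with podiatrist as the cluster. Use arm, the other week's adherence, sensor-recorded wearing time and baseline covariates. Then average the two weeks, apply the 80% cut-off, fit the planned GLMM in each imputed data set and pool.
4. Add a sensitivity analysis that counts missing as non-adherent, because the imputation itself assumes data missing at random.

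The cost is revised wording and moderate programming. The auxiliary data are already planned: sensors log wearing time over the 12 months separately from the activity monitor, and baseline characteristics are recorded at inclusion. No further visits or consent are needed.

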### Plans to give access to the full protocol, participant level-data, and statistical code {31c}

The full protocol, pseudonymized dataset, and statistical code will be available on request after the results of the study have been published.

### Oversight and monitoring

#### Composition of the coordinating center and trial steering committee {5d}

This is a multicentered study designed, performed, and coordinated at the University of Twente, Voetmax Orthopedie, and Voetencentrum Wender. Support for the trial is provided by the following:
Principal investigator: takes supervision of the trial.Coordinating investigator: preparation of protocol and revisions, ethics committee application, trial registration, visits the podiatrists and pedorthists during the start-up phase, organizes the MI-trainings given by MI-trainers to podiatrists, supports the logistics for patient accrual, take informed consents, monitors inclusion of patients, coordinates study visits, repeated measurements and collection of log data from sensors, organizes data acquisition, collection and storage, analyses and manages the primary and secondary outcome data, prepares the first draft of the manuscripts, and prepares progress reports for the project team/steering committeeProject team/steering committee: design of the study, check study progress and approve protocol amendments and recommendations, and approve publication of study reports; meets monthlyStudy physicians (podiatrists/pedorthist): identify potential recruitments and take informed consent if possiblePatient experience experts: advice project team during the inclusion periodAdvisory board: discuss the findings and implementation strategy with the project team and with the international network of the advisory board

#### Composition of the data monitoring committee, its role, and reporting structure {21a}

Because of the low burden and minimal risks, no data monitoring committee was appointed. The investigators are responsible for procedures of data monitoring.

#### Adverse event reporting and harms {22}

Adverse events are defined as any undesirable experience occurring to a participant during the study, whether or not considered related to the trial procedure. Because this trial was exempt from full medical ethical approval, all adverse events reported spontaneously by the participants or observed by the podiatrist, pedorthist, or the investigator or her staff will be registered by the investigator in the Excel database, and consequences will be discussed in the project team. As always, it is possible that problems may arise with the participant’s feet or orthopedic shoes, for which the participant will receive usual care performed by the podiatrist and/or pedorthist (see the “Relevant concomitant care permitted or prohibited during the trial {11d}” section).

#### Frequency and plans for auditing trial conduct {23}

To facilitate compliance with Good Clinical Practice guidelines, the investigator will permit study-related monitoring, audits, and inspections by authorized organizations. Aspects that will be monitored may include inclusion rate, informed consent progress, inclusion and exclusion criteria, trial master file, source data verification, safety reporting, trial procedures, and closing and reporting. Given the low risk of the intervention and because this trial was exempt from full medical ethical approval, extensive auditing is not considered necessary. Therefore, no audits are planned at this time as the principal investigator will be present to oversee all study activities as data are being collected.

#### Plans for communicating important protocol amendments to relevant parties (e.g., trial participants, ethical committees) {25}

Amendments are defined as changes made to the research. This trial was exempt from full medical ethical approval by the CMO region Arnhem – Nijmegen according to the Dutch Law. The study protocol was subsequently reviewed and approved by de Ethical Committee of the BMS faculty of the University of Twente. Therefore, all substantial amendments will only be notified to the Ethical Committee of the BMS faculty of the University of Twente. Non-substantial amendments will be recorded and filed by the sponsor. The online trial registry will be updated accordingly, and changes will be communicated in the publication of the results of this study.

#### Dissemination plans {31a}

It is our intention to publish the findings of the study in (medical) scientific journals and to present them at scientific meetings. The responsibility for publications and presentations lies with the investigators. Only those investigators making a significant contribution to the study design and/or the collection, analysis, or interpretation of the study data will be eligible for authorship. No restrictions regarding the public disclosure and publication of the research data have, or will be made, by the funder.

## Discussion

Currently, there is little knowledge about the effectiveness of interventions, and the cost-effectiveness of the novel care approach (motivational interviewing combined with digital shoe-fitting) has not been studied at all [29]. Therefore the aim of this randomized controlled trial is to assess the (cost-)effectiveness of this novel care approach compared to usual care in terms of adherence to wearing orthopedic shoes and ulcer prevention. Since the start of including the first participants in our study, we improved and modified our initial protocol based on operational and logistic issues and new insights; the most important changes are described and explained below.

As in any trial, patient recruitment is crucial. Based on the abovementioned power analysis the required sample size, including the loss to follow-up, for this study was estimated at 220 participants. These participants were to be included in a period of 9 months throughout The Netherlands. However, for practical reasons, it was not feasible to include throughout The Netherlands, and therefore inclusion will only take place in the east of The Netherlands. Because of this change and the outbreak of COVID-19, the goal of 220 participants is no longer realistic with the initially defined criteria and design in the intended period. In order to include as many participants as possible, we were forced to make some changes to the original study protocol.

First, we no longer include only patients receiving their first pair of orthopedic shoes, but we also include patients who already had orthopedic shoes and are eligible for a new pair of orthopedic shoes. Therefore, the pedorthist is now also actively involved in participant recruitment.

Second, due to this new role of the pedorthist, the background assignment of the treating podiatrist (being trained in MI or not) no longer determines the shoe-fitting procedure by the pedorthist. Each pedorthist has his/her own procedure of shoe-fitting: the new digital shoe-fitting procedure or the casting-based shoe-fitting procedure. In addition, the existing last is also used for an extra pair of orthopedic shoes, and thereby the shoe-fitting procedure is already determined for each subsequent pair of orthopedic shoes. However, the background assignment of the treating podiatrist remains leading over the shoe-fitting procedure with regard to which group the participant belongs to (intervention or control group), because most participants have been treated by the same podiatrist for years and we do not want to change that for this study. The participants in the intervention group will have an appointment with their podiatrist or one of the other MI-trained podiatrists to perform motivational interviewing before or as soon as possible after they receive their first or new pair of orthopedic shoes.

Last, the second group of 12 additional podiatrists received MI training, and 16 podiatrists have been added to the control group to further increase inclusion. Because the inclusion in the intervention group lagged behind the control group, the second group of podiatrists, who received MI training, consists of the podiatrists who see most patients with diabetes. This is in contrast to the original group of podiatrists, who were assigned to one of the groups based on stratified randomization.

In addition, a few small changes to the number of study consultations have also been made: 1) We reduced the number of six consultations that the participants would have with one of the investigators by two consultations. The investigator sees the participant at the delivery of the orthopedic shoes (T0), and 3 months (T1), 6 months (T2), 9 months (T3), and 12 months (T4) after the participant received their orthopedic shoes. 2) As a result of this change, the participants will receive the activity monitor during T1 (3 months) and T2 (6 months) instead of T1 (2 to 4 weeks) and T3 (4 months) as shown in Table 2. 3) All participants will be asked to fill in the MOS 6 months after receiving their orthopedic shoes, also the participants who will be approached for a second in-depth interview. 4) During every consultation with one of the investigators, the participant will be asked if they have an ulcer or have had an ulcer in the last 3 months. If so, the participant will be asked to fill in the iPCQ.

In conclusion, this trial aims to assess the (cost-)effectiveness of this novel care approach compared to usual care in terms of adherence to orthopedic shoes and ulcer prevention. The outcomes of this trial will generate insights into the socio-economic impact of the novel care approach on adherence to orthopedic shoes. These are crucial steps toward better ulcer prevention in high-risk diabetes patients.

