### Assignment of interventions: allocation

#### Sequence generation {16a}

Randomization will be performed at the level of the podiatrists. Based on their working location (distance from Voetmax Orthopedie locations), working calendar, working days, and number of patients with diabetes, we included 20 podiatrists of Voetencentrum Wender in this study. Since the podiatrists still differ widely in their number of patients seen and experience with the specific target group, stratified randomization will be used for the group of podiatrists. Four of the 20 podiatrists run special consultations for people with diabetes and are therefore likely more specialized in diabetic foot disease. These four podiatrists are split into two groups, based on the number of patients seen per year (based on the figures of 2019), and equally randomized to the group who receive MI training or to the group who do not receive MI training. The other 16 podiatrists are randomized next, also stratified by the number of patients seen per year (based on four strata using last year’s figures). The randomization is done centrally by an independent researcher using www.sealedenvelope.com.

Each podiatrist will exclusively provide either the MI intervention or usual care. Thereafter, the pedorthist will provide the new digital shoe-fitting procedure for the intervention group of participants or the casting-based shoe-fitting procedure for the control group.

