#### Concealment mechanism {16b}

The participants have not randomized themselves, because the background assignment of the treating podiatrist (being trained in MI or not) will determine the treatment allocation of the participants. Randomization is performed at the level of the podiatrists to avoid contamination between intervention and control participants. Therefore, the randomization sequence will not be concealed from the podiatrists. Because each podiatrist will exclusively provide either the MI intervention or usual care, and thereafter, the pedorthist will provide the new digital shoe-fitting procedure for the intervention group of participants or the casting-based shoe-fitting procedure for the control group, and the randomization sequence will also not be concealed from the pedorthists.

All participant data is pseudonymized, but because the investigators have access to the coding of the personal data of the participants, the randomization sequence will also not be concealed from them.

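### 28 of the 48 podiatrists lie outside the randomisation, yet one pooled intention-to-treat model and the label 'randomised' cover all of them, leaving the primary estimate open to confounding of unknown size and direction

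*Protocol article*

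**What the plan says.** Under Sequence generation {16a} the article states that "we included 20 podiatrists of Voetencentrum Wender in this study". It gives the reason for stratifying: "Since the podiatrists still differ widely in their number of patients seen and experience with the specific target group, stratified randomization will be used". The four podiatrists who run special diabetes consultations are handled first; the other 16 are then stratified by annual patient numbers.

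The Discussion, under the changes made since the trial began, reports that "the second group of 12 additional podiatrists received MI training, and 16 podiatrists have been added to the control group to further increase inclusion". Because intervention inclusion was lagging, "the second group of podiatrists, who received MI training, consists of the podiatrists who see most patients with diabetes". The article draws the contrast itself: "This is in contrast to the original group of podiatrists, who were assigned to one of the groups based on stratified randomization".

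The analysis sections carry no trace of this change. Under Primary study outcome: "A logistic link function will be used for the binary outcome on participant level (adherent yes/no) and random effects for podiatrists will be included". Under the section on protocol non-adherence and missing data {20c}, the primary comparison "will be tested in an intention-to-treat analysis using a generalized linear mixed model (GLMM) which can inherently deal with data missing at random". Neither section distinguishes randomised from added podiatrists. Trial design {8} still names a cluster-randomised controlled trial, and the opening of the Discussion still speaks of a randomised controlled trial.

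**The concern.** The sponsor judged volume and experience important enough to stratify on. In the second wave, diabetes volume was instead used to decide which podiatrists received MI training. In that wave, arm and volume are therefore linked by construction.

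A podiatrist random intercept accounts for correlation among patients of the same podiatrist. It assumes that the podiatrist effects are unrelated to arm. Randomisation justifies that assumption for the first 20 podiatrists, and nothing in the design justifies it for the others. If patients of high-volume podiatrists would adhere differently anyway, the difference passes into the arm coefficient.

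At stake is what the primary estimate means. Followed as written, the plan yields one pooled number under the name of a randomised intention-to-treat comparison, although more than half of its clusters were not randomised.

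**Working it through.** **1. The plan's own sample size.** Inputs from Sample size {14}: 40% versus 60%, two-sided alpha 0.05, power 0.80, intraclass correlation 0.01. The article does not give the cluster size used; I take 200/20 = 10 per randomised podiatrist.

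- Per arm without clustering: (1.960 + 0.842)² × (0.24 + 0.24) / 0.20² = 94.2
- Design effect: 1 + (10 − 1) × 0.01 = 1.09
- Total: 2 × 94.2 × 1.09 = 205, within 3% of the stated 200; power at 200 is 0.79

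The stated figure reproduces, so this point does not rest on a sample-size error.

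**2. Share of clusters outside the randomisation.**

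- Added podiatrists: 12 + 16 = 28
- All podiatrists: 20 + 28 = 48
- Share: 28/48 = 58%

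If the original 20 split 10:10 (the article does not say so for all 20), the added shares are 12/22 = 55% in the MI arm and 16/26 = 62% in the control arm. These are close, so wave alone is not strongly tied to arm. The problem lies inside the second wave, where volume helped to set the arm.

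**3. Illustration of size, under no true effect.** The documents give no figure for the prognostic gap or for participants per podiatrist. I assume:

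- Adherence differs by 5 to 10 points between patients of high-volume and other podiatrists.
- High-volume podiatrists supply 80% of intervention participants and 30-50% of control participants, so the shares differ by 0.30 to 0.50.

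Spurious difference = gap × difference in shares:

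- Low end: 0.05 × 0.30 = 1.5 points
- High end: 0.10 × 0.50 = 5 points

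Standard error: the article's dropout of 10/171 = 5.8% leaves 220 × 0.942 ≈ 207 evaluable, or 103.5 per arm. With 220/48 ≈ 4.6 per podiatrist the design effect is 1 + 3.6 × 0.01 = 1.036. Then SE = √(2 × 0.24 × 1.036 / 103.5) = 0.069.

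Two-sided error rate = 1 − Φ(1.96 − b/SE) + Φ(−1.96 − b/SE), where b is the spurious difference:

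| b (points) | b/SE | error rate |
|---|---|---|
| 0 | 0 | 5.0% |
| 1.5 | 0.22 | 5.5% |
| 3 | 0.43 | 7.2% |
| 5 | 0.72 | 11.1% |

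The 207 assumes that the full 220 are recruited, which the Discussion itself doubts.

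**4. Precision of a randomised-only estimate.** The article does not say how many participants the 20 randomised podiatrists supply. For a range of totals N, with N/20 per podiatrist and the assumptions of step 1, power = Φ(0.20/SE − 1.96):

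| N from the 20 | power |
|---|---|
| 60 | 0.35 |
| 100 | 0.52 |
| 150 | 0.68 |
| 200 | 0.79 |

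**The case against.** The strongest reply is that the departure is openly disclosed, that the article promises to communicate changes in the results publication, and that covariates and sensitivity analyses normally belong to an analysis plan that is not shown. All of this is true. It bars any claim of concealment, and it means that the absence of a covariate list is not itself an error. It does not answer the point. The article states a design, a primary model, an intention-to-treat claim and a label, and after the change these no longer fit together. Covariates in an unseen plan would not restore randomisation for the added podiatrists.

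A reader might also infer more than the documents support:

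- *That the effect is biased, or biased in favour of MI.* Nothing in the article links podiatrist volume to shoe adherence. The stratifier (patients seen per year) and the selection criterion (patients with diabetes) may not even be the same measure.
- *That the article rules out adjustment.* It names the link function and the random effect; it does not say that no other term will enter.
- *That the 16 added controls are stated to be non-randomised.* This is a strong inference from the high-volume podiatrists having been taken for MI and from the contrast with the original group. It is not an explicit statement.
- *That arm is confounded with calendar period.* Podiatrists were added to both arms in similar proportions, and no dates are given.
- *That recruitment produced different patients by arm.* The article says that "the randomization sequence will not be concealed from the podiatrists" and that intervention inclusion lagged. Slower inclusion alone does not show a different patient mix, and pedorthists now recruit too.

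**Conclusion.** The point stands as an exposure to confounding, not as a demonstrated bias. That the 12 added MI podiatrists were selected rather than randomised is explicit; for the 16 added controls it is inferred. Together they make 28 of 48 clusters. The stated pooled analysis and the randomised label were not brought into line with that change.

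The consequence for the estimate is unknown in size and direction. The error rates of about 5.5-11% depend wholly on the assumed gap and shares and only show that a modest imbalance would matter. If volume and experience carry no prognostic weight, the bias is zero. The need to separate and relabel the estimates does not depend on those figures.

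**What to change.** Before the data are analysed:

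1. Report the primary mixed model restricted to participants of the 20 randomised podiatrists, and reserve the word 'randomised' for that estimate.
2. Report beside it the full-cohort model with fixed effects for wave (randomised or added), podiatrist volume and diabetes specialisation. Add participant covariates recorded at inclusion, such as risk profile, ulcer and amputation history, previous orthopedic-shoe use, age and sex.
3. Obtain volume and specialisation for the added podiatrists on the same definitions; the article documents them only for the original 20.
4. Describe the full cohort as partly non-randomised in the design statement and in the results.
5. State that second-wave arms may overlap too little in volume for adjustment to remove confounding. A wave term does not help within that wave, and a volume term may rest on extrapolation.

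The cost is wording, one further model and some data on the added podiatrists. The real price is precision: if the 20 randomised podiatrists supply 100 participants, power for the planned difference is about 0.52. The headline claim becomes more modest, which is the reason to show both estimates, each correctly named. Trial status says that inclusion was still ongoing, so the change could be made ahead of the analysis.
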